#### Primary outcomes

Participants will be classified as either responders or non-responders, where a responder is a participant who achieves their target RAASi dose with no post-randomisation serum potassium measurements ≥5.6 mmol/L. Participants who discontinue the study before completion will be deemed as missing.

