### Statistical analysis and sample size

#### Summary of baseline data and flow of patients

We will perform an intention-to-treat analysis. The primary outcome (i.e. responder / non-responder status) will be analysed via χ^2^ test with α = 0.05. The proportion of responders in each arm, the difference thereof, and the 95% confidence interval for the difference in proportions will be reported.

Additional analyses may be performed to explore the consistency of the effect across subgroups, for instance defined by the degree of MRA and/or ACEi/ARB treatment at baseline. Provided the modelling assumptions are satisfied (e.g. sufficient numbers of responders / non-responders in each arm), these will be done by logistic regression.

If there is loss to follow-up, sensitivity analysis will be conducted. Given the binary nature of the primary outcome, extreme scenarios such as the worst case in the intervention group (all losses to follow-up classified as non-responders) and the best case in the control group (all losses to follow-up are responders) will be considered.

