#### Sample size estimation

Clinical evidence suggests that the proportion of patients reaching the target dose of RAASi in the control arm would be around 50% as a conservative estimation based on our experience. The study is powered to detect an effect size of the intervention of around 30%.

Group sample sizes of 52 will achieve approximately 90% power to detect a difference between the group proportions of 0.3 using a two-sided Z-test with pooled variance and a two-sided χ^2^ test. The proportion of responders in the placebo arm is assumed to be 0.5 with the corresponding proportion in the active arm 0.8 under the alternative hypothesis. The significance level (α) of the test is 0.05. This results in a total of 104 patients required and, accounting for 20% loss to follow-up, we will recruit 130 patients to be randomised to each group.

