## Discussion

This trial will be the first to look at the use of SZC for the maximisation of RAASi dosing in CKD patients. Our hypothesis is that SZC therapy will reduce the incidence of treatment-limiting hyperkalaemia in CKD-HF patients, allowing higher doses of RAASi therapy and therefore better clinical outcomes. Achievement of the participant’s target RAASi dose is the primary endpoint, and secondary endpoints include measures to assess safety in terms of hyperkalaemia, cardiovascular risk in terms of troponin T levels [19, 20], and efficacy in terms of time-to-target dose. We will also assess the impact of achieving target RAASi dosing on hospital admission rates and duration of stay, with the hope that optimum RAASi treatment will translate into reduced morbidity and improved QoL.

The strengths of the study include its randomised, double-blind design, and the favourable safety profile of the trial drug. We intend that the design will provide high-quality evidence that, if our hypothesis is supported, will help guide changes in clinical practise. As SZC is approved for the treatment of hyperkalaemia in the UK and has a favourable safety profile, our study has the benefit of being low-risk to participants.

The side-effect profile of SZC is minimal and hence we hope that adherence to the study protocol will be satisfactory. Our statistical predictions have nonetheless accounted for a 20% dropout rate owing to participants’ decisions, movements out of the area, death, progression to renal transplant, or other causes. Our study design focusses on a single recruitment centre.

The novel value of this study centres around (I) its examinations of SZC to limit hyperkalaemia and allow RAASi maximisation in the under-studied combined CKD-HF patient group, and (ii) its expansion of the currently limited safety data on the use of RAASi therapy in advanced CKD patients. The joint CKD-HF clinic approach is an emerging practise, and, if clinical benefit is proven, we would hope to investigate future studies with wider scope for more extensive population validity.

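### The missing-data sentence removes participants from the primary test even when their non-response is already recorded, which can bias the comparison in either direction

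*Protocol article*

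**What the plan says.** Protocol article, Primary outcomes: "a responder is a participant who achieves their target RAASi dose with no post-randomisation serum potassium measurements ≥5.6 mmol/L". The sentence that follows reads: "Participants who discontinue the study before completion will be deemed as missing".

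The analysis section (Summary of baseline data and flow of patients) says "We will perform an intention-to-treat analysis" and "The primary outcome (i.e. responder / non-responder status) will be analysed via" a chi-square test. It names no imputation for that test. If there is loss to follow-up, it plans extreme scenarios, for example "the worst case in the intervention group (all losses to follow-up classified as non-responders) and the best case in the control group".

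Sample size estimation sizes the test on 52 per group, "to detect a difference between the group proportions of 0.3 using a two-sided Z-test with pooled variance", and enlarges the total from 104 to 130 for 20% loss. The Discussion attributes that 20% to participants' decisions, "movements out of the area, death, progression to renal transplant, or other causes".

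**The concern.** The responder definition has two parts, and the potassium part can only be failed once. After one value at or above the threshold, nothing later can make the participant a responder, so the primary outcome is known from that visit. The next sentence turns this known outcome into a missing one if the participant then leaves the study. Because the primary test uses responder status with no imputation, the person is dropped.

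For these participants the rule conflicts with the intention-to-treat statement: an outcome was observed in a randomised person and is not used. Removing failures raises the apparent response rate of the arm that loses them, so the comparison depends on who leaves each arm. The same group is mishandled in the named sensitivity scenario, where a placebo participant with a recorded failure who leaves would be counted as a responder.

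Death is among the listed causes of dropout, so deaths also appear to become missing. The article does not say so directly.

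**Working it through.** **Inputs from the article.** Placebo 0.5, active 0.8, 52 per group after losses, 20% loss, 130 in total (65 per arm at 1:1), and "The significance level (α) of the test is 0.05", two-sided with pooled variance. Who leaves, and why, is not given. Every loss pattern below is an assumption.

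**Formula.** With n per arm, rates p0 and p1, and mean rate p̄:

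power = Φ{[(p1 − p0) − 1.96·√(2p̄(1 − p̄)/n)] / √([p0(1 − p0) + p1(1 − p1)]/n)}

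**1. The plan's own figure.** For n = 52, 0.5 vs 0.8: (0.300 − 1.96 × 0.0935)/0.0888 = 1.31, so power is 90.6%. Also 104/0.8 = 130. Both stated figures reproduce.

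**2. Effect of dropping leavers.** 65 randomised per arm, 13 leave each arm, and the true rates among all randomised are 0.5 and 0.8 (32.5 and 52 responders).

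- *Leaving unrelated to outcome in both arms.* Completers show 0.50 vs 0.80. There is no bias and power is 90.6%.
- *Placebo losses all recorded failures, active losses unrelated to outcome.* Placebo reads 32.5/52 = 0.625 and active stays 0.80. The difference is 0.175. Power: (0.175 − 1.96 × 0.0888)/0.0871 = 0.01, so 50.5%.
- *Losses in both arms all failures.* Placebo reads 32.5/52 = 0.625 and active 52/52 = 1.00. The difference is 0.375, larger than the true 0.30.
- *A milder case: three quarters of placebo losses are non-responders, active losses unrelated to outcome.* Placebo losses contain 13 × 0.25 = 3.25 responders, so placebo reads (32.5 − 3.25)/52 = 0.5625. The difference is 0.2375 and power is about 75%.
- *No true effect (0.5 vs 0.5), active losses all non-responders, placebo losses unrelated to outcome.* Completers show 0.625 vs 0.50, and the test wrongly favours active in 24.8% of trials instead of 2.5%. With the pattern reversed, it wrongly favours placebo equally often.

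**3. The named worst/best-case check.** Completers at 0.8 vs 0.5, loss L in each arm, 65 per arm. Active becomes 0.8(1 − L) and placebo 0.5(1 − L) + L.

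| L | Active | Placebo | Power |
|---|---|---|---|
| 5% | 0.760 | 0.525 | 81% |
| 10% | 0.720 | 0.550 | 52% |
| 20% | 0.640 | 0.600 | 7% |

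**4. Cost of keeping recorded failures.** Completers at 0.8 vs 0.5 (41.6 and 26 responders), 13 leavers per arm, and a share f of leavers with a recorded failure. The analysed n is 52 + 13f, with rates 41.6/n and 26/n.

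| f | Active | Placebo | Power |
|---|---|---|---|
| 0 | 0.800 | 0.500 | 90.6% |
| 0.5 | 0.711 | 0.444 | 84.1% |
| 1 | 0.640 | 0.400 | 78.9% |

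The last row is the limit in which every loss is a failure.

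**The case against.** Several points on the other side are sound.

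- Analysing available outcomes by randomised arm, with extreme-case sensitivity analyses, is a common way to treat outcomes that are truly unobserved, and the sample size is built for it. A reader might infer that the whole analysis breaks intention-to-treat. The text supports that only for participants whose status is already determined.
- The rule concerns leaving the study. The IMP dosage table stops or changes study drug according to potassium, and RAASi may be down-titrated for hypotension. Neither is described as ending participation, and someone who stops the drug but stays is still classified. That hyperkalaemia leads people to leave is plausible but not stated.
- The listed causes include moving away and transplant, which need not relate to outcome. The 20% is a planning allowance for roughly two months of participation, not an observed rate.
- A reader might infer that the worst/best-case check would overturn any realistic positive result. That holds only near 20% loss. At 5% the check keeps about 81% power. The article also offers that scenario as an example, so others are not excluded, and it leaves further missing-data handling open.

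These points limit the size and certainty of the bias. None of them alters the primary classification, which has no exception for a failure already observed.

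**Conclusion.** The point holds in its narrow form. As written, the plan discards recorded primary-endpoint failures when the participant later leaves, and the named control-arm scenario would count some of them as responders. This is fixed in the article's outcome definition, so it is not a detail left to a statistical analysis plan.

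Neither the direction nor the size of the bias can be known from the document. Bias is absent if leaving is unrelated to outcome. Under the assumed patterns at 20% loss, a true 30-point difference could be analysed as anything from 17.5 to 37.5 points. The lower figure requires active-arm losses to be unrelated to outcome; if they too are all failures, the bias reverses. It would therefore be wrong to say that the rule favours one arm, or that it necessarily costs power.

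The treatment of deaths is inferred from joining the Discussion to the outcome definition, and needs to be made explicit.

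**What to change.** Replace the sentence under Primary outcomes with: *Any participant with a recorded post-randomisation potassium of 5.6 mmol/L or more is a non-responder regardless of later discontinuation; only participants whose status is undetermined are missing.* Apply the same rule in the sensitivity scenarios, so that no recorded failure is relabelled as a response. State how a death before the target dose is classified.

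Add a sensitivity analysis that counts all undetermined participants as non-responders in both arms. The new sentence does not settle how the undetermined are handled: failure can be recorded early while success needs the target dose, so leaving them out can still tilt the rates. Multiple imputation by arm or a tipping-point grid is a reasonable option here, though not the only one.

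The cost is a change of wording and slightly more analysis, with no new data. The estimate may be less favourable. In the limit where every loss counts as a failure, the planning rates become 40% vs 64% and power at 65 per arm is about 79%. The change should be made before unblinding, so that it cannot appear driven by results.

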#### Secondary outcomes

Responder / non-responder classification, where a responder is defined as a patient who achieved maximum dose of MRA *and* ACEi/ARB with serum potassium ≤5.6 mmol/L;Responder / non-responder classification, where a responder is defined as a patient who achieved maximum dose of MRA and or ACEi/ARB and serum potassium ≤6.0 mmol/L;Time from randomisation to hyperkalaemia (serum potassium ≥5.6 mmol/L);Time from randomisation to severe hyperkalaemia (serum potassium > 6.0 mmol/L);Number of RAASi dose escalations per patient;Final doses of ACEi/ARB, MRA;Change in QoL score, eGFR, ACR, BNP, serum sodium, troponin T at event / end as compared to baseline;Number of hospital admissions per patient, as well as duration of hospital admissions;Within-patient change in serum potassium as compared to baseline;

### Statistical analysis and sample size

#### Summary of baseline data and flow of patients

We will perform an intention-to-treat analysis. The primary outcome (i.e. responder / non-responder status) will be analysed via χ^2^ test with α = 0.05. The proportion of responders in each arm, the difference thereof, and the 95% confidence interval for the difference in proportions will be reported.

Additional analyses may be performed to explore the consistency of the effect across subgroups, for instance defined by the degree of MRA and/or ACEi/ARB treatment at baseline. Provided the modelling assumptions are satisfied (e.g. sufficient numbers of responders / non-responders in each arm), these will be done by logistic regression.

If there is loss to follow-up, sensitivity analysis will be conducted. Given the binary nature of the primary outcome, extreme scenarios such as the worst case in the intervention group (all losses to follow-up classified as non-responders) and the best case in the control group (all losses to follow-up are responders) will be considered.

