### Randomisation

Participants will be randomised 1:1 to either the placebo or active (SZC) arm of the trial. Randomisation is stratified by patients’ baseline RAASi dose at the start of the trial (individuals on < 50% standard dose vs those on ≥50% standard dose) to ensure equal proportions of RAASi therapies in each group.

We will use the REDCap Randomisation Module (https://wiki.uiowa.edu/display/REDCapDocs/REDCap+Randomization+Module). This module can be turned on by selecting the “Enable the randomization module” checkbox during project creation or after. This would preserve the randomisation procedure independent of the study statistician.

Randomisation will be implemented by the research pharmacy at St George’s. Randomisation codes will be generated by the study statistician on an external spreadsheet. The research pharmacy will be informed by the study team as soon the patient is consented, and will use the randomisation list to assign the participant to their allocated arm. In the case of an adverse event or patient safety issue, emergency unblinding will be performed by the on-call research pharmacist.

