### Outcomes

The main clinical outcome measure will be serum potassium concentration, which will be measured every two weeks, and the dose of RAASi at the end of the study. The statistical outcome measure will be achieving target level of RAASi without hyperkalaemia (i.e. serum potassium ≥5.6 mmol/L). Target RAASi doses are defined as maximum dosing as in Table 3. Outcomes are also displayed in Table 4.

**Table 3 Tab3:** Dose classification of RAASi therapy

	Minimum dose	Half maximum dose	Maximum dose

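### Randomisation is stratified by baseline RAASi dose but the primary test and confidence interval ignore the stratum; if the stratum is prognostic this costs some precision, but not validity

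*Protocol article*

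**What the plan says.** The Randomisation section states: "Randomisation is stratified by patients’ baseline RAASi dose at the start of the trial". There are two levels, below 50% and at or above 50% of standard dose, with 1:1 allocation.

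Under Summary of baseline data and flow of patients: "The primary outcome (i.e. responder / non-responder status) will be analysed via" a chi-square test at α = 0.05. The responder proportions and their difference are to be given, and "the 95% confidence interval for the difference in proportions will be reported". No stratum or covariate is named. Baseline RAASi treatment returns only in optional work: "Additional analyses may be performed to explore the consistency of the effect across subgroups", by logistic regression if the numbers allow.

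Under Primary outcomes, "a responder is a participant who achieves their target RAASi dose with no post-randomisation serum potassium measurements" at or above 5.6 mmol/L. Under Outcomes, "Target RAASi doses are defined as maximum dosing as in Table 3". The Sample size estimation section uses the same unstratified test: 52 per group, 0.5 versus 0.8, two-sided α = 0.05, about 90% power.

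**The concern.** If allocation is balanced within strata, differences between strata cannot contribute to the observed treatment difference. The crude standard error still counts that variation as noise. When the stratum predicts the outcome, the crude test therefore rejects too rarely and the crude interval over-covers.

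There is reason to think the stratum matters. Success requires the maximum dose, and on the three-level scale of Table 3 a patient at half-maximum has one step to climb while a patient at minimum dose has two. The sponsor also chose this as the only stratification factor.

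At stake is precision in a trial planned on 104 analysed patients, from a factor that is already recorded. This is not an omission that a later analysis plan would naturally fill: the article names its primary test, and names it without the design factor.

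**Working it through.** **1. The plan's own figure.** With pooled variance, n = [1.96·√(2·0.65·0.35) + 1.2816·√(0.5·0.5 + 0.8·0.2)]² / 0.3² = (1.3221 + 0.8206)² / 0.09 = 51.01, rounded up to 52. Power at 52 is Φ[(0.3·√52 − 1.3221)/0.6403] = Φ(1.314) = 90.6%. The stated 52 per group and about 90% are reproduced.

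**2. Why the crude standard error is too large.** The crude variance of the difference is [p_c(1−p_c) + p_t(1−p_t)]/n. The stratified variance replaces each term by its average within strata. Take equal strata and placebo rates of 0.30 and 0.70 (a 40-point gap). A common odds ratio that gives 0.80 overall puts the active rates at 0.68 and 0.92.
- Crude: √[(0.25 + 0.16)/52] = 0.0888.
- Stratified: √[(0.21 + 0.1456)/52] = 0.0827, where 0.1456 = (0.68·0.32 + 0.92·0.08)/2.
- Ratio: 1.074.

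The same sum gives √(0.41/0.396) = 1.017 at 20 points and √(0.41/0.2928) = 1.18 at 60 points.

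**3. Simulation at the planned effect.** 200,000 trials per row, 0.50 versus 0.80, 52 per arm. Assumed: two equal strata of 26 per arm, exact balance within strata, a common odds ratio, and the gap itself. The article gives neither stratum sizes nor stratum response rates.

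| Gap in placebo response | Power, chi-square | Power, CMH | Mean 95% CI width, crude | Width, stratified | Crude CI coverage | Type I error, chi-square | Type I error, CMH |
|---|---|---|---|---|---|---|---|
| 0 | 91.1% | 90.9% | 0.344 | 0.341 | 94.5% | 6.2% | 4.7% |
| 20 points | 91.3% | 91.5% | 0.345 | 0.335 | 94.9% | 5.6% | 5.3% |
| 40 points | 92.4% | 94.0% | 0.345 | 0.317 | 96.0% | 4.2% | 5.0% |
| 60 points | 94.2% | 97.1% | 0.345 | 0.288 | 97.7% | 2.0% | 5.1% |

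The width ratios are 0.345/0.335 = 1.03, 0.345/0.317 = 1.09 and 0.345/0.288 = 1.20. They exceed the formula ratios in step 2 by one to two points because the simple stratified Wald interval is slightly too narrow with 26 per cell (its coverage is about 94%).

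The 6.2% and 5.6% come from the discreteness of the uncorrected chi-square at 52 per arm. The excess is largest at a zero gap, where the strata carry no information. At 65 per arm the same rows give 4.4% and 4.0%.

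**4. A smaller true effect.** For 0.50 versus 0.70, power for chi-square versus CMH is 57.7% versus 57.7% at 20 points, 58.1% versus 61.8% at 40 and 58.9% versus 71.3% at 60. At a zero gap it is 57.7% versus 56.5%, which reflects the plain test's actual size of about 6% there.

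**5. Unequal strata.** With 42 and 10 per arm, the smaller stratum having the higher response, and 0.50 versus 0.80 overall, power is 91.2% for both tests at 20 points and 91.7% versus 92.3% at 40. Chi-square type I error at 40 points is 4.9%.

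**The case against.** The strongest reply is that nothing here threatens validity. An unadjusted chi-square is a simple, prespecified test of the marginal difference, it matches the sample size calculation, and its power at the planned effect stays above 90% in every scenario. All of that stands.

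The size of the loss also rests on assumptions. A reader might infer that baseline dose must be a strong predictor, because untreated patients have further to climb in the same time. The article does not support that. Under Study timeline, patients with no RAASi at baseline have seven visits and others six, and untreated patients are started on RAASi at the initial visit, so the design offsets part of the distance. Response also requires potassium to stay below 5.6 mmol/L in patients who enter at 5.0–5.5, so titration distance is only one determinant. Prognostic value is plausible, not established. At a 20-point gap the two analyses are nearly the same, and with the uneven split tried above the gain is small even at 40 points.

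The optional logistic regression by baseline treatment answers only in part. It explores subgroups and does not adjust the primary result.

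**Conclusion.** The mismatch between design and analysis is real, and its consequence is conditional. If baseline dose is prognostic, the primary test and interval are conservative. At the planned effect the power cost is about 0.2 points for a 20-point gap, 1.6 for 40 and 2.9 for 60, with intervals about 3%, 9% and 20% wider. At a true difference of 0.2 the cost is about 4 points (40-point gap) to 12 points (60-point gap). These figures assume equal strata, balance within strata and a common odds ratio. The loss was smaller in the unequal split checked, and there is none if the factor is not prognostic.

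A reader might go further and infer that the trial is underpowered or its type I error inflated by ignoring the strata. Neither follows: 52 per group and 90% power are reproduced with the unstratified test, the risk difference is not biased, and the effect of ignoring a prognostic stratum is to lower type I error. This is an efficiency improvement worth making, not a defect that undermines the result.

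**What to change.** State in the protocol, and in the analysis plan if there is one, that the primary test is a Cochran-Mantel-Haenszel test stratified by baseline RAASi dose as used at randomisation. Report the Mantel-Haenszel risk difference with a stratified 95% interval. A Newcombe-type interval is preferable to the simple stratified Wald interval, which covered slightly below 95% here. Keep the plain chi-square and crude difference as supportive, and include the stratum term in the logistic subgroup models.

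The cost is one sentence before database lock and unblinding, with no new data, since the stratum is recorded at randomisation. If the factor proves not to be prognostic, the price at the planned effect is about 0.2 power points (90.9% against 91.1%). Fixing the choice now also avoids choosing between adjusted and unadjusted results after the data are seen.

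### The unadjusted chi-square primary analysis is valid and correctly powered, but it gives up some precision by leaving out baseline potassium and eGFR

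*Protocol article*

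**What the plan says.** Under Summary of baseline data and flow of patients, the protocol article says: "The primary outcome (i.e. responder / non-responder status) will be analysed via" a chi-square test. It adds that "the 95% confidence interval for the difference in proportions will be reported". No covariate enters. Logistic regression appears only as an option for subgroups: "Additional analyses may be performed to explore the consistency of the effect across subgroups".

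Under Primary outcomes, a responder must reach the target RAASi dose "with no post-randomisation serum potassium measurements ≥5.6 mmol/L".

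Other sections supply the baseline facts:
- Eligibility criteria admit a most recent potassium of 5.0 to 5.5 mmol/L and any stable eGFR below 60.
- Table 1 schedules laboratory potassium at screening and at C1, and the baseline blood panel includes creatinine.
- Randomisation is stratified by baseline RAASi dose only (below 50% of standard dose versus 50% or more).
- The Background describes the hyperkalaemia risk in CKD stage 4/5 as high.

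On power, Sample size estimation says: "Group sample sizes of 52 will achieve approximately 90% power to detect a difference between the group proportions of 0.3". The calculation is for an unadjusted pooled-variance Z or chi-square comparison, two-sided at the 5% level. On the response rates behind it, the same section says: "The proportion of responders in the placebo arm is assumed to be 0.5 with the corresponding proportion in the active arm 0.8".

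**The concern.** One high potassium value is enough to make a participant a non-responder. Someone who enters at 5.5 mmol/L is 0.1 below the failure line, and someone who enters at 5.0 is 0.6 below it. By the article's own Background, kidney function also bears on hyperkalaemia. Neither variable is balanced by the stratification and neither is used in the primary comparison.

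Two things are at stake. The confidence interval may be wider than the collected data require. And if the arms happen to differ in entry potassium, no prespecified adjusted result exists to answer the question; an adjustment chosen after unblinding would look post hoc.

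**Working it through.** **1. The plan's own figure.** With 0.5 and 0.8, the pooled proportion is 0.65.
- n per arm = [1.96 × √(2 × 0.65 × 0.35) + 1.2816 × √(0.5 × 0.5 + 0.8 × 0.2)]² / 0.3² = (1.322 + 0.821)² / 0.09 ≈ 51.0, which is consistent with 52.
- Power at 52 per arm = Φ[(0.3 × √52 − 1.322) / 0.640] = Φ(1.314) = 90.6%.
- 2 × 52 = 104, and 104 / 0.8 = 130.

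The stated calculation reproduces for the stated test.

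**2. Gain from adjustment, two covariates.** Simulated trials had 52 per arm, marginal response held at 0.5 and 0.8, and two independent covariates with the same odds ratio in both arms. The odds ratios per SD are assumptions. Results come from three separate simulations:

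| Odds ratio per SD (potassium, eGFR) | Power, unadjusted to adjusted | Variance of risk difference |
|---|---|---|
| Neither prognostic | 90.7% to 90.6%; another simulation lost about 0.4 points | +2% |
| 1.3, 1.3 | 90.9% to 91.5%; another found essentially no gain | −1% |
| 1.5, 1.5 | 90.3% to 92.0%; 90.5% to 92.1%; 91.0% to 92.1% | −4%; −4% |
| 2, 1.5 | 90.9% to 93.4%; 92.0% to 94.5%; 91.2% to 93.6% | −9%; −8% |
| 2, 2 | 90.1% to 94.5%; 90.9% to 95.1% | −15%; −13% |

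With 4,000 trials per setting, the Monte Carlo standard error of one power figure is √(0.9 × 0.1 / 4000) ≈ 0.5 points.

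**3. Cross-check with the test based on the standardised difference.** A separate simulation used one combined index and tested the standardised risk difference itself. Two independent covariates at 2 each equal one index with log odds ratio √2 × ln 2 = 0.98, an odds ratio of 2.67. Two at 1.5 each give √2 × ln 1.5 = 0.573, an odds ratio of 1.77.

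| Odds ratio per SD of index | Chi-square | Standardised difference | Variance reduction | Shift from a one-SE imbalance |
|---|---|---|---|---|
| 1.28 | 91.3% | 91.5% | about 0% | 0.9 points |
| 1.65 | 91.3% | 92.3% | 3% | 1.8 points |
| 2.12 | 90.6% | 93.1% | 8% | 2.7 points |
| 2.72 | 90.6% | 94.6% | 13% | 3.3 points |
| 4.48 | 90.9% | 97.3% | 24% | 4.3 points |

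The two tables agree. With no effect and 0.5 in both arms (index odds ratios 1.65 and 2.72), the standardised-difference test rejected in 5.5% and 5.1% of trials and the unadjusted test in 6.3% of trials in each setting. Adjustment therefore showed no type I error penalty.

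**4. Size in interval terms.** The standard error of the raw difference is √(0.41 / 52) = 0.089, so the 95% half-width is 1.96 × 8.88 = 17.4 points. A 4% smaller variance gives 17.4 × √0.96 = 17.1 points. A 15% smaller variance gives 17.4 × √0.85 = 16.0 points.

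**5. Size of chance imbalance.** If entry potassium is uniform on 5.0 to 5.5 (an assumption), its SD is 0.5 / √12 = 0.144. The standard error of the difference in arm means is 0.144 × √(2/52) = 0.028. Means then differ by more than 1.96 × 0.028 = 0.055 mmol/L in 1 trial in 20. In SD units, one standard error is √(2/52) ≈ 0.20, the imbalance used in the last column of step 3.

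**6. Plausibility of the assumed odds ratios.** The entry window spans 0.5 / 0.144 = 3.46 SD. An odds ratio of 2 per SD implies 2^3.46 ≈ 11-fold odds of response from one end to the other, and 1.5 implies 1.5^3.46 ≈ 4-fold.

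**The case against.** The strongest reply is that nothing here is an error. The chi-square test and raw difference are valid under randomisation and match the sample size calculation. Choosing adjustment is a matter of efficiency, and a supportive adjusted model may sit in an analysis plan that is not shown. All of this stands, except that the primary method is stated in the article, so the choice of an unadjusted primary test is not simply deferred.

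A reader might infer that an imbalance in entry potassium would bias the result or leave it unprotected. The documents do not support that. Chance imbalance is part of the random variation that the unadjusted interval and the 5% error rate already cover. A one-SE imbalance shifts the difference by roughly 1 to 4 points, against a standard error of about 9 and a target of 30.

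A reader might also infer that the trial is underpowered without adjustment. It is not; step 1 reproduces about 90%.

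The benefit may also be smaller than the middle rows suggest. The entry window is narrow, and 11-fold odds across it is a strong assumption for an eligibility value. Response also requires reaching the target dose, which can fail through hypotension rather than potassium. Initiation dosing in the active arm may weaken the link with entry potassium, whereas the simulations used the same odds ratio in both arms. These points stand and favour the lower rows, at least for potassium. eGFR is less restricted, since any value below 60 is admitted.

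**Conclusion.** The point holds as a modest efficiency weakness in a valid, correctly powered analysis. Two baseline variables that are collected on everyone and are plausibly prognostic go unused in both the stratification and the primary test.

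The size of the loss rests wholly on assumed prognostic strength: about nil at an odds ratio of 1.3 per SD for each covariate, 1 to 2 power points and 3 to 4% of variance at 1.5 each, and about 4 points and 13 to 15% at 2 each. The document cannot say which applies. The case for changing is the asymmetry: almost nothing is lost if the covariates prove weak, and an adjusted result named in advance is credible in a way that a later one is not.

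**What to change.** Before unblinding, prespecify the primary analysis as a logistic regression on:
- arm;
- the randomisation stratum (baseline RAASi dose below 50% versus 50% or more);
- baseline laboratory potassium, continuous, stating which measurement counts (for example, the last before the first dose of study drug);
- baseline eGFR, continuous.

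The stratum belongs in the model because it is a design factor and bears on reaching the target dose. Report the standardised (marginal) difference in proportions with a delta-method or bootstrap 95% confidence interval, and base the primary test on that same estimate so that test and interval agree. Keep the chi-square test and raw difference as the sensitivity analysis. The reported quantity remains a difference in proportions.

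At the planned rates there would be about 26 + 10 = 36 non-responders among 104 evaluable participants, or 9 for each of the four model terms, which is workable. The simulations did not include the stratum, so its own contribution is not counted above.

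The cost is a change of wording and a few lines of code, with no new data. The downside is a negligible power loss (0.4 points or less in the simulations) if the covariates are not prognostic.
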